## Abstract

**Background:**

The emergence and increased spread of microbial resistance is a major challenge to all health care systems worldwide. In primary care, acute respiratory tract infection (ARTI) is the health condition most strongly related to antibiotic overuse.

**Objective:**

The RESIST program aims at optimizing antibiotic prescribing for ARTI in German primary care. By completing a problem-orientated online training course, physicians are motivated and empowered to utilize patient-centered doctor-patient communication strategies, including shared decision making, in the treatment of patients with ARTI.

**Methods:**

RESIST will be evaluated in the form of a nonrandomized controlled trial. Approximately 3000 physicians of 8 (out of 16) German federal states can participate in the program. Patient and physician data are retrieved from routine health care data. Physicians not participating in the program serve as controls, either among the 8 participating regional Associations of Statutory Health Insurance Physicians (control group 1) or among the remaining associations not participating in RESIST (control group 2). Antibiotic prescription rates before the intervention (T0: 2016, 1st and 2nd quarters of 2017) and after the intervention (T1: 3rd quarter of 2017 until 1st quarter of 2019) will be compared. The primary outcome measure is the overall antibiotic prescription rate for all patients insured with German statutory health insurance before and after provision of the online course. The secondary outcome is the antibiotic prescription rate for coded ARTI before and after the intervention.

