### Recruitment

Recruitment of participating physicians is undertaken in 8 German federal states and regions (Bavaria, Baden-Wuerttemberg, Lower Saxony, North Rhine, Westphalia-Lippe, Brandenburg, Mecklenburg-Western Pomerania, and Saarland), assisted by the respective regional Association of Statutory Health Insurance Physicians. General practitioners, primary care pediatricians, and practice-based otorhinolaryngologists can enroll in the RESIST program on a voluntary “first-come, first-served” basis. The maximum number of participating physicians per region is related to the size of the regional association. In total, we aim to include up to 3000 physicians in the program.

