### Participants

Physicians successfully completing the RESIST online training course are compared to nonparticipating physicians.

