### Sample Size

With respect to the primary outcome, a reduction of the physicians’ overall antibiotic prescription rate by 1% is assumed for RESIST (from 33.8% in the control group 1 to 32.8% in the intervention group). Without consideration of cluster effects, 2 × 34,865 patients are needed to show this effect with a power of 80% and a type I error of 5% (two-sided). Assuming an intracluster correlation (ICC) of 8% [16] and an average cluster size of 160 patients per practice, a design effect of 13.72 is determined. Overall, the sample size increases to 2 × 478,400 patients (956,800 patients in total). Thus, 2 × 2990 practices (5980 in total) are needed for the evaluation.

For the secondary outcome, a reduction of 3% in the physicians’ antibiotic prescription rate for ARTI is expected (from 30.5% in the control group 1 to 27.5% in the intervention group). Assuming a power of 80% and a type I error of 5% (two-sided), 2 × 3590 patients are required. With an ICC of 8% [16] and an average cluster size of 127 patients (diagnosed with ARTI) per practice, the sample size increases to 2 × 39,751 patients (79,502 patients in total). Hence, 2 × 313 practices are needed (626 practices in total). The sample size necessary to investigate the effect of the intervention on the primary outcome will be adequate to investigate its effect on the secondary outcome as well.

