### Ethical Approval and Consent to Participate

The evaluation was approved by the ethics committee at Rostock University Medical Center in June 2017 (Reference: A 2017-0090). Participating physicians provide written informed consent. However, no informed consent is necessary from the patients, as pseudonymized and de facto anonymized routine data are used based on §80 SGB X.

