## Discussion

With up to 3000 physicians participating in the program, RESIST is among the largest real-world interventions aiming at reducing inadequate antibiotic prescribing for ARTI in primary care. Long-term follow up of up to 21 months will allow for investigating the sustainability of the intervention.

As RESIST utilizes an open-label nonrandomized evaluation concept, potential bias has to be carefully addressed. Bias may arise from the fact that physicians most interested in reducing inadequate antibiotic prescriptions are also likely to be those most motivated to take part in RESIST. To counteract this, we make use of an attractive incentivization and reimbursement scheme. In addition, the inclusion of comparable practices not participating in the program (both among participating regions and among those not participating in RESIST) allows for control of this potential source of bias.

We will also minimize bias due to changed coding. For example, a clinically identical patient treated with antibiotics might be coded with lower respiratory tract infection initially but with pneumonia after the intervention, leading to an overestimation of the interventional effect. By measuring the overall antibiotic prescribing rate of antibiotics without regard to any specific disease as the primary outcome measure, we can exclude bias due to coding phenomena.

Last but not least, the RESIST program joins the ranks of other current initiatives to reduce inadequate antibiotic prescribing. Thus, contamination effects between the projects are possible. However, by including a high number of physicians and practices among half of all German states, we believe to be able to address this potential source of bias adequately.

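### T1 starts on a fixed calendar date directly after T0, although exposure begins at each physician's own course completion, so some untrained time is likely to count as post-intervention

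*Protocol article*

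**What the plan says.** The Abstract (Methods) and the Study Design section define two calendar windows. The first is given as "Antibiotic prescription rates before the intervention (T0: 2016, 1st and 2nd quarters of 2017". The second is given as "after the intervention (T1: 3rd quarter of 2017 until 1st quarter of 2019) will be compared". No transition or training quarter lies between them.

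Under Recruitment, physicians "can enroll in the RESIST program on a voluntary “first-come, first-served” basis". Under Participants, "Physicians successfully completing the RESIST online training course are compared to nonparticipating physicians". The Intervention section describes three modules of about one hour each. The practice materials follow once the course is passed, and a one-time allowance is paid on successful completion.

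The Statistical Methods section specifies a negative binomial model for the annual number of prescriptions, with the number of patients as offset and the pre-RESIST prescription rate as a covariate. It names no term for when a physician completed the course. The Discussion adds: "Long-term follow up of up to 21 months will allow for investigating the sustainability of the intervention".

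**The concern.** The windows are set by calendar and are common to all. Exposure is set by an individual event, passing the course. If everything up to 30 June 2017 really precedes the intervention, the training must fall inside the period labelled as after it. A participant's quarters before completion then count as post-intervention although the training and its materials had not yet reached that physician.

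The expected result is a contrast biased toward no effect. This threatens the size of the estimate and the power, and it does not create a false positive. It also weakens the sustainability aim, because sustainability is a matter of time since training and a fixed window does not measure that.

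**Working it through.** **1. The windows.** T0 is the four quarters of 2016 plus two of 2017, six quarters in all. T1 is Q3 2017 to Q1 2019: 2 + 4 + 1 = 7 quarters, or 21 months. T1 begins the day after T0 ends.

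**2. Where training can fall.** There are three possibilities.
- Inside T1, as the labels imply: part of T1 is untrained, and the contrast is diluted.
- Inside T0: the intervention group's baseline rate already contains some of the effect. Adjusting for that rate tends to remove part of the effect again.
- Clustered at the boundary: neither problem is material.

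Nothing in the article shows that the third case applies. One nearby date is in the ethics section: "The evaluation was approved by the ethics committee at Rostock University Medical Center in June 2017". That is the last month of T0. It fits training from Q3 2017 onward but does not prove it.

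**3. The plan's own sample size.** Inputs from the Sample Size section: rates "from 33.8% in the control group 1 to 32.8% in the intervention group", two-sided 5%, power 80%, ICC 0.08, 160 patients per practice.
- n per group = [1.96 √(2 × 0.333 × 0.667) + 0.8416 √(0.338 × 0.662 + 0.328 × 0.672)]² / 0.01² = 34,866 (stated: 34,865).
- Design effect = 1 + 159 × 0.08 = 13.72.
- 34,865 × 13.72 = 478,348. Divided by 160 this is 2989.7, so 2990 practices; 2990 × 160 = 478,400.

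The stated figures reproduce.

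**4. Illustration of dilution.** Let f be the share of T1 before completion. With the seven quarters weighted equally, no effect before completion and the full effect after it, the expected effect is 1.0 × (1 − f) points. The effective number per group is 478,400 / 13.72 = 34,869. The standard error is √[(0.338 × 0.662 + 0.328 × 0.672) / 34,869] = 0.00357. Power ≈ Φ(0.01 × (1 − f) / 0.00357 − 1.96).

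If completions are spread evenly over the first k quarters of T1, then f = (k/2)/7 = k/14.

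| Spread over first k quarters | f | Effect (points) | Power, 2 x 2990 practices | Practices per group for 80% |
|---|---|---|---|---|
| 0 | 0 | 1.00 | 80% | 2990 |
| 1 | 1/14 | 0.93 | 74% | 3470 |
| 2 | 1/7 | 0.86 | 67% | 4074 |
| 4 | 2/7 | 0.71 | 52% | 5873 |
| 6 | 3/7 | 0.57 | 36% | 9186 |

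The article supplies neither k nor f, so the table is a range and not an estimate.

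**The case against.** The case on the other side is substantial, and several parts of it stand.

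- **No dates are given.** A reader might infer that physicians are shown to have enrolled and finished during T1. The article does not say so. First-come enrolment describes order, not timing. Funding was approved in December 2016 and the course takes about three hours, so early or clustered completion is possible. Follow-up of up to 21 months describes follow-up, not completion, and could even mean time counted from each physician's own start. This stands: the timing is an inference from the window labels.
- **A pooled seven-quarter outcome is not stated.** The model uses annual counts. If the outcome year were the last four quarters, completions in the first three quarters of T1 would cause no dilution. This stands, and it makes the power figures illustrative.
- **The assumed 1-point reduction may already allow for roll-out.** The Sample Size section attributes it to RESIST without saying. This also stands.
- **Fixed windows answer a legitimate question.** The primary outcome compares rates before and after the courses were provided, and common calendar quarters protect against seasonal differences between groups. A reader might infer that the estimate answers no stated question; that goes too far.
- **The detail may be in the full protocol or analysis plan.** How completion quarters are handled could be set out there. But the article itself fixes the windows, the group definition and the model, and those three do not fit together as stated.

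What the objection does not remove is the abutting windows. Unless training clustered at the boundary, either T1 contains untrained time or T0 contains trained time, and both tend to weaken the estimate.

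**Conclusion.** The point holds as a mismatch between calendar windows and individual exposure, with a likely bias toward no effect. Its extent cannot be derived from the article and may be negligible.

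The fall in power from 80% to about 67%, 52% or 36% shows how sensitive the plan would be if 1/7, 2/7 or 3/7 of T1 were untrained. It is not a demonstrated loss. It rests on equal weight for the seven quarters, no effect before completion and a full effect after it, 1.0 point as the effect in fully trained time, equal groups, one physician per practice, and a two-proportion approximation instead of the planned regression. Seasonal prescribing would change the weights.

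A separate, secondary matter is that the intervention group consists of physicians who completed the course. Any who enrolled but did not finish belong clearly to neither group. A reader might infer a known bias in the opposite direction. The article reports no such physicians, so its presence and size are unknown; the Discussion acknowledges selection on motivation in general terms.

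**What to change.** 1. Report the distribution of completion quarters. Because an allowance is paid on completion, the dates should be on record.
2. Choose one of two definitions of post-intervention time, using completion dates only and without looking at prescribing results.
   - Exclude a common roll-out period from T1 in both groups. For example, analyse Q2 2018 to Q1 2019: these four quarters match the annual count in the model and contain each calendar quarter once.
   - Alternatively, start post-intervention time in the quarter after completion, with controls contributing the same calendar quarters.
3. Report the full fixed-T1 analysis alongside.
4. As a secondary step, add a sensitivity analysis that counts all enrolled physicians, including any non-completers, as intervention.

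**Cost.** Fewer post-intervention quarters are analysed. The common exclusion is the cheaper choice. Physician-specific starts require linking completion quarters to data aggregated by practice and assigning index quarters to controls, and they need care with unequal seasonal mixes. The article states that data analysis began in February 2020, so the change should be dated and reported as made after that point.

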**Results:**

RESIST is publicly funded by the Innovations funds of the Federal Joint Committee in Germany and was approved in December 2016. Recruitment of physicians is now completed, and a total of 2460 physicians participated in the intervention. Data analysis started in February 2020.

**Conclusions:**

With approximately 3000 physicians participating in the program, RESIST is among the largest real-world interventions aiming at reducing inadequate antibiotic prescribing for ARTI in primary care. Long-term follow up of up to 21 months will allow for investigating the sustainability of the intervention.

**Trial Registration:**

ISRCTN Registry ISRCTN13934505; http://www.isrctn.com/ISRCTN13934505

**International Registered Report Identifier (IRRID):**

RR1-10.2196/18648

## Introduction

### Background

Growing microbial resistance is a major challenge of all health care systems worldwide. The overuse and misuse of antibiotics in human and veterinary medicine accelerates this development [1,2]. In primary care, acute respiratory tract infection (ARTI) is the health condition most strongly related to antibiotic overuse [3,4]. This is a striking fact, as most cases of ARTI are caused by viruses and/or are self-limiting [5-7]. Considerable geographical variations in antibiotic prescribing for ARTI exist. In Europe, prescribing rates for ARTI range from below 40% in the Netherlands, Scandinavia, and Germany to up to 60% in the United Kingdom and Ireland, and reach up to almost 80% in southern Europe [8]. Reasons for inadequate prescribing include the physician’s overestimation of patient expectations toward antibiotic treatment as well as a deceptive “safety culture” in certain cases [9,10].

A considerable number of interventions to reduce inadequate prescribing for ARTI have been developed and evaluated. Overall, the main intervention strategies applied to date include laboratory and point of care testing (POCT), provider or patient education, computerized clinical decision support, prescribing feedback, delayed prescribing, and communication training. There is now sufficient evidence for the effectiveness of communication skills training and laboratory testing/POCT to reduce antibiotic prescribing for ARTI [11,12]. In addition, there is evidence that the effect of these interventions differs according to the level of antibiotic prescribing for ARTI in a given setting. High-prescribing countries benefit from laboratory testing/POCT, whereas medium- and low-prescribing countries show higher effects for communication training [12].

In parallel to the design and evaluation of interventional approaches, an increasing number of nations and supranational bodies have started initiating programs of antimicrobial stewardship. These usually include public information campaigns, education for health care providers, local surveillance of antibiotic resistance, and the provision of research grants to generate evidence necessary to improve antimicrobial stewardship [13]. Along with these initiatives, the German DART 2020 strategy was developed. Apart from strengthening a One Health approach to antimicrobial stewardship by addressing both human and veterinary medicine, supporting research is a major aim of the initiative. In this context, since 2016, the German *Innovationsfonds* granted several programs and trials addressing antimicrobial stewardship. The RESIST program is one of these programs. Within the program, approximately 3000 physicians of 8 (out of 16) German federal states can participate in online training aiming at patient-centered medical care for patients suffering from ARTI. Nationally and internationally, RESIST is one of the largest scientifically evaluated health intervention programs conducted to date. This protocol describes how the program is being evaluated.

### Objectives

RESIST aims at optimizing antibiotic prescribing for ARTI in German primary care. By completing a problem-orientated online training course, physicians are motivated and empowered to utilize patient-centered doctor-patient communication strategies, including shared decision making, in the treatment of patients with ARTI. Additionally, the courses provide current data on microbial resistance development and on rational antibiotic use. Moreover, physicians receive information materials for their patients as well as regional prescribing feedback. Based on this protocol, we are assessing whether the RESIST program reduces the number of antibiotics prescribed and, in the case of antibiotic use, impacts the choice of substance. The primary outcome measure is the antibiotic prescription rate for all patients insured with German statutory health insurance before and after provision of the online course. The secondary outcome is the antibiotic prescription rate for coded ARTI before and after the intervention. In addition, using individual qualitative interviews and focus group discussions, the perspective and perceptions of patients, physicians, and practice staff on the program will be evaluated.

## Methods

### Study Design

As RESIST is primarily a real-world project aiming to address as many participants as funding allows, it is evaluated in the form of a nonrandomized controlled trial. Patient and physician data are retrieved from routine health care data used by the Central Research Institute of Ambulatory Health Care in Germany (Zi). The Zi continuously analyzes prescription and diagnoses data on behalf of all German regional Associations of Statutory Health Insurance Physicians. The data analyzed include information on diagnosis as coded in practices and prescriptions as collected in pharmacies. Physicians not participating in the program serve as controls, either among the 8 statewide participating Associations of Statutory Health Insurance Physicians (control group 1) or among the federal states not eligible for participation in RESIST (control group 2). Antibiotic prescription rates before the intervention (T0: 2016, 1^st^ and 2^nd^ quarters of 2017) and after the intervention (T1: 3^rd^ quarter of 2017 until 1^st^ quarter of 2019) are compared.

### Recruitment

Recruitment of participating physicians is undertaken in 8 German federal states and regions (Bavaria, Baden-Wuerttemberg, Lower Saxony, North Rhine, Westphalia-Lippe, Brandenburg, Mecklenburg-Western Pomerania, and Saarland), assisted by the respective regional Association of Statutory Health Insurance Physicians. General practitioners, primary care pediatricians, and practice-based otorhinolaryngologists can enroll in the RESIST program on a voluntary “first-come, first-served” basis. The maximum number of participating physicians per region is related to the size of the regional association. In total, we aim to include up to 3000 physicians in the program.

### Participants

Physicians successfully completing the RESIST online training course are compared to nonparticipating physicians.

### Blinding

Participating physicians are not blinded as they enroll voluntarily in the RESIST program.

### Intervention

The intervention is based on an online training course consisting of three modules. Each module can be completed within approximately 1 hour. Module 1 focuses on patient-centered doctor-patient communication, and points to typical communicative situations when treating patients with ARTI. Within the module, physicians are encouraged to reflect upon these situations and to question perceived pressure to prescribe antibiotics. Modules 2 and 3 deal with rational antibiotic use in the case of upper and lower respiratory tract infections. After passing the Continued Medical Education–accredited course, physicians receive posters and brochures on rational antibiotic use to display them in their practices or to use them during consultations. Physicians successfully completing the course receive a one-time allowance. In addition, physicians receive further reimbursement for up to 20 patients with ARTI per quarter, which they document as treated according to the strategies adopted after participating in the online training. In addition, participating physicians receive a feedback report on aggregated data on regional antibiotic prescribing patterns. Figures are compared between intervention and control groups. See Multimedia Appendix 1 for more details on each component and module of the intervention [14].

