### Control Group

Physicians not participating in the program serve as controls, either among the 8 participating regional Associations of Statutory Health Insurance Physicians (control group 1) or among the remaining associations not participating in RESIST (control group 2).

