### Outcomes

The primary outcome measure is the overall antibiotic prescription rate of all patients insured with a German statutory health insurance before and after the provision of online courses. Secondary outcomes are (a) the antibiotic prescription rate for ARTI in patients aged ≥ 1 year before and after the intervention; (b) the antibiotic prescription rate based on different types of ARTI (eg, otitis media, bronchitis, pneumonia; see Table 1) before and after the intervention in patients aged ≥ 1 year; and (c) quality of antibiotic prescribing for ARTI measured by internationally accredited quality indicators of the European Surveillance of Antimicrobial Consumption Project (ESAC) [15], again before and after the intervention.

**Table 1 table1:** International Classification of Diseases codes relevant for diagnosing acute respiratory tract infection.

Code	Diagnosis
J00	Acute nasopharyngitis (common cold)
J01	Acute sinusitis
J02	Acute pharyngitis
J03	Acute tonsillitis
J04	Acute laryngitis and tracheitis
J06	Acute upper respiratory infections of multiple and unspecified site
J09	Influenza due to identified zoonotic or pandemic influenza virus
J10	Influenza due to identified seasonal influenza virus
J11	Influenza, virus not identified
J12	Viral pneumonia, not elsewhere classified
J13	Pneumonia due to *Streptococcus pneumoniae*
J14	Pneumonia due to *Haemophilus influenzae*
J15	Bacterial pneumonia, not elsewhere classified
J16	Pneumonia due to other infectious organisms, not elsewhere classified
J17	Pneumonia in diseases classified elsewhere
J18	Pneumonia, organism unspecified
J20	Acute bronchitis
J21	Acute bronchiolitis
J22	Unspecified acute lower respiratory infection
J40	Bronchitis, not specified as acute or chronic
H65	Nonsuppurative otitis media
H66	Suppurative and unspecified otitis media

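### Payment per documented ARTI patient goes to trained physicians only and could enlarge the ARTI-coded denominator of the secondary outcomes in one group; the stated safeguard against coding bias covers the primary outcome only.

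*Protocol article*

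**What the plan says.** All places are in the protocol article.

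- **Payment.** Under Intervention, besides a one-time allowance, "physicians receive further reimbursement for up to 20 patients with ARTI per quarter, which they document as treated according to the strategies adopted" in the course. Under Control Group, "Physicians not participating in the program serve as controls", and no comparable payment is described for them.
- **Outcome.** Under Objectives, "The secondary outcome is the antibiotic prescription rate for coded ARTI before and after the intervention". Under Outcomes, item (a) is "the antibiotic prescription rate for ARTI in patients aged" 1 year or older, item (b) splits it by type of ARTI, and item (c) covers ESAC quality indicators for ARTI prescribing.
- **Source of the diagnosis.** Under Study Design, the data hold "information on diagnosis as coded in practices and prescriptions as collected in pharmacies".
- **Model.** Under Statistical Methods, the primary model is a negative binomial regression of prescription counts, with the number of patients as offset and the earlier prescription rate as a covariate. The secondary models take the same form.
- **Safeguard.** The Discussion accepts that changed coding can exaggerate the effect. Its example is a patient moved from one respiratory diagnosis to another. Its remedy is the primary outcome, which ignores diagnosis, and it concludes that by this means "we can exclude bias due to coding phenomena".

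**The concern.** The payment depends on documenting patients with ARTI, it starts after the course, and it reaches one group only. The secondary outcomes rest on ARTI diagnoses recorded by the same practices. If the payment, or the closer attention to ARTI that comes with it, led trained physicians to code cases that would otherwise have gone uncoded, the denominator would grow in the intervention group alone. Adjustment for the rate at T0 cannot remove a change that begins after T0.

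The Discussion considers recoding between ARTI types but not an increase in the number of patients coded as ARTI, and its remedy leaves outcomes (a) to (c) uncovered. The ARTI rate is the outcome closest to the programme's aim, so an unexamined shift in its denominator would weaken the most relevant secondary result.

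**Working it through.** **Inputs.** From Sample Size: the ARTI rate is assumed to change "from 30.5% in the control group 1 to 27.5% in the intervention group"; ICC 0.08; 127 ARTI patients per practice, time window not stated. From Intervention: a cap of 20 paid patients per quarter. From Study Design: T1 runs from the third quarter of 2017 to the first quarter of 2019, which is 7 quarters. Assumed, because the article gives neither: x, the extra ARTI-coded patients per practice, and q, their antibiotic rate.

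**1. The plan's own figure.** The article states: "Assuming a power of 80% and a type I error of 5% (two-sided), 2 × 3590 patients are required". A two-proportion calculation with pooled variance gives 3591. The design effect is 1 + (127 − 1) × 0.08 = 11.08. Then 3590 × 11.08 = 39,777 and 39,777 / 127 = 313.2 practices; 313 × 127 = 39,751 is the stated number per group. The figures reproduce, and they show that the planned unit for this outcome is the ARTI-diagnosed patient.

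**2. Dilution with prescribing unchanged.** Apparent rate = (0.305 × 127 + q·x) / (127 + x), where 0.305 × 127 = 38.7 treated patients.

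| x | q = 0 | q = 10% | q = 30.5% |
|---|---|---|---|
| 2 | 30.0% | 30.2% | 30.5% |
| 5 | 29.3% | 29.7% | 30.5% |
| 10 | 28.3% | 29.0% | 30.5% |
| 20 | 26.4% | 27.7% | 30.5% |

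**3. Shift that would reproduce the whole 3-point effect.**
- q = 0: x = 127 × (0.305 / 0.275 − 1) = 13.9, or +10.9%.
- q = 10%: x = 127 × (0.305 − 0.275) / (0.275 − 0.10) = 3.81 / 0.175 = 21.8, or +17%.

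**4. Chance of a significant result from dilution alone (q = 0).** This uses a two-proportion test at the effective size, number of practices × 127 / 11.08, as an approximation to the planned model. With 313 practices per group it is 19% for x = 5, 54% for x = 10 and 80% for x = 13.9. With 2460 per group (assuming one physician per practice and an equal control group) it is 23% for x = 2 and 85% for x = 5.

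**5. Room under the cap.**
- If 127 is a quarterly count, the cap is 20 / 127 = 16% of it.
- If 127 is annual, the cap is 80 / 127 = 63%.
- Only if 127 covers more than 127 / 20 = 6.35 quarters, nearly all of T1, does the cap (20 × 7 = 140) exceed the patients already coded.

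**6. What an all-patient denominator would show.** ARTI prescriptions per patient = (ARTI prescriptions per ARTI patient) × (ARTI patients per patient). A real fall with stable coding gives 0.275 / 0.305 = 0.902 on both scales. Pure dilution with q = 0 gives 0.902 × 1.109 = 1.00 on the all-patient scale. With q = 10% and x = 21.8, ARTI-coded prescriptions rise by 2.18 / 38.7 = 5.6%. The two explanations therefore separate.

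**The case against.** The strongest objection is that the causal link is not in the article. The payment is for patients documented as managed in the trained way, not for ICD codes or additional cases. Nothing says that the payment record feeds the diagnosis data, or that mild ARTI goes uncoded. The detailed description of the components is in an appendix that is not shown. On a quarterly or annual reading of the 127, an average practice could fill the cap from patients it already codes, which leaves little reason to code more. All this stands, so a reader may not infer that coding did or will rise. The comparison with the cap is itself uncertain, because the cap is per physician and the 127 per practice.

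Three further points stand:

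- **Size and direction.** The 14 and 22 are solved backwards from the 3-point effect and are not forecasts. If the added patients were treated at 30.5% there would be no fall. A bias in the programme's favour is plausible but not demonstrated.
- **Visibility.** A reader might infer that the programme would look successful even if no antibiotic were withheld. The article does not support that: the only confirmatory comparison uses the primary outcome, which would not improve and would stand beside the ARTI rate.
- **Denominator.** The offset of the secondary models is not spelled out, and with all patients as offset this dilution would not arise. However, the outcome's wording and the cluster size of 127 patients diagnosed with ARTI point to ARTI-coded patients.

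Exact offsets and extra sensitivity analyses may well be left to an analysis plan. What remains is that the article itself raises coding bias, offers a remedy that reaches the primary outcome only, and overlooks a one-sided incentive within its own intervention.

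**Conclusion.** The point holds as a possible bias in the ARTI-coded secondary outcomes. It is not a demonstrated bias, and the confirmatory primary outcome is not affected by this mechanism. It rests on three assumptions: that the secondary denominator is ARTI-coded patients, that the payment or the programme leads to additional coding, and that the added patients receive antibiotics less often than 30.5%. Under these, an increase in coded patients of 10.9% (untreated) to 17% (10% antibiotic rate) would equal the whole planned effect, and with about 2460 practices per group far smaller shifts could reach significance. How likely any such shift is cannot be judged from the article.

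A reader might conclude that the per-ARTI rate should be replaced as the secondary outcome, or interpreted only when coding shows no group difference. Neither follows. ARTI-coded prescriptions per all patients still depend on coding and answer a different question, and at this size a trivial coding difference could be significant. The case supports an inexpensive added check and a narrower statement in the Discussion.

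**What to change.** Keep the rate per ARTI patient as the secondary outcome, and add:

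1. A model of ARTI-coded patients per all insured patients of the practice, by group, adjusted for the T0 value and reported with its 95% CI.
2. A sensitivity analysis of antibiotic prescriptions for ARTI with all patients of the practice as the offset.

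Attribute a fall in the per-ARTI rate to changed prescribing only if it agrees with the sensitivity analysis and the primary outcome, and if the coding shift is too small to explain it. Judge that on the confidence interval, not on non-significance. As a yardstick, a rate ratio of 0.902 could be produced entirely by untreated additions only if the coding ratio reached 1 / 0.902 = 1.109. Apply the same check to outcome (b) and to any ESAC indicator with an ARTI-coded denominator. In the Discussion, limit the statement on excluding coding bias to the primary outcome.

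**Cost.** One or two extra models per outcome. The Data Collection and Statistical Methods sections already list ARTI diagnoses, prescriptions, group and number of patients. Because analysis began in February 2020, the models must be labelled as added. The all-patient rate shows a smaller absolute effect and still depends partly on coding, for example if treated patients are recoded out of ARTI.
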